#### Phase 4: Follow-Up

Four months after the conclusion of exposure to SH+ intervention, women who have given consent will be invited to participate in a semistructured interview to investigate their experience of using ALBA and the TreC research app to understand how the women felt during the intervention. In addition, the long-term effects of stress will be collected by administering a follow-up questionnaire.

### Participant Recruitment and Withdrawal

#### Overview

The study will take place in the Province of Trento (North Italy), where approximately 5000 women have or have had a diagnosis of BC, with almost 500 new cases every year [27]. In January 2018, the Breast Unit was established in the Province of Trento. It represents an innovative organizational model that merges various professionals, structures, and services transversally to make it more effective and homogeneous and coordinates the clinical path of patients with BC.

Recruitment will target women diagnosed with BC who are enrolled in the Breast Unit program, with additional support from local voluntary associations where possible. A convenience sampling approach will be used. Textbox 1 [14,17,28-30] outlines the study’s inclusion and exclusion criteria.

Inclusion and exclusion criteria.
**Inclusion criteria**
Have a diagnosis of stage 0, I, II, or III breast cancer (BC)Be a female patient under the care of the Breast UnitBe aged ≥18 years (Italian legal age)Have a smartphone with internet access and the ability to download the app and be able to use itBe a resident of the Autonomous Province of TrentoKnow and understand the Italian languageHave a moderate level of psychological distress, defined by a score between 15.9 and 29.9 on the Kessler Psychological Distress Scale, with higher scores indicating more severe distress [28]. This range aligns with the inclusion thresholds used in World Health Organization (WHO) studies using the RESPOND protocol [17].Have a general well-being score of ≥3 on the General Health Questionnaire, consistent with the inclusion criterion used in World Health Organization studies using the Self Health Plus protocol [14].Obtain a score between 30 and 80 (cutoffs identified based on the literature on the Short Form Health Survey 36 [SF-36] instrument in patients diagnosed with BC [29,30]) on the “Mental health” scale of the SF-36 questionnaire.
**Exclusion criteria**
Patients unable to provide informed consent (prerequisite for participation in the study)Inadequate understanding of the Italian languagePatients aged >75 yearsWomen with metastatic BC (stage IV), those in the metastatic phase, receiving palliative care, or with a life expectancy of <1 yearObtain a score <30 on the “Bodily Pain” scale of the SF-36, indicating severe pain levels [29,30]Suicidal tendencies, depression, or other psychiatric diagnosesAlready receiving psychological or psychotherapeutic care at the time of recruitment

Health professionals at the Breast Unit will verify the inclusion and exclusion criteria related to the sociodemographic data (phase 0), while psychologists will assess the psychological screening data (phase 1).

Participants will be required to sign an informed consent form during recruitment (phase 0), following a comprehensive explanation of the project, its objectives, data collection, management, processing procedures, the required level of involvement, the study duration, and confidentiality matters. They will be informed that they can withdraw from the study at any time without providing a reason and that doing so will not affect the quality of their care or interfere with their treatment. Informed consent must be given freely and in writing, accompanied by a data processing authorization form, before joining the study. Participants must provide written informed consent. They will also receive a privacy policy statement explaining how their personal data will be processed during the study and must provide explicit consent for its use. Copies of the informed consent and privacy forms will be provided to participants and available in a dedicated section of the app.

To promote participant engagement and retention throughout the 6-week intervention, specific features were designed to sustain interest and minimize dropout, such as incorporating gamification elements, providing regular feedback or progress tracking, scheduling personalized reminders, and offering small recognition for continued participation. No monetary compensation was provided.

#### Sample Size

This research project is designed as a POC study, where a limited sample is sufficient to achieve the intended aims. On the basis of calculation assuming a nonnormal distribution and using nonparametric statistics, a sample of 24 women with BC diagnoses is sufficient when applying a Bonferroni-corrected significance level (α=.025) to control for type I error and multiple comparisons. Nevertheless, to validate this estimate, the sample calculation was run with the Power Analysis and Sample Size 2021 (NCSS, LLC) and Stata (StataCorp LLC) programs. The resulting sample size is 41 participants, based on the following assumptions: a significance level (α) of .025, statistical power of 0.80 (to ensure sufficient sensitivity to type 2 error), a mean difference between groups (eg, pre- and postintervention questionnaires) of 1.00, an expected effect size (δ) of 0.50, and an SD of 2.00.

The chosen effect size (Cohen *d*=0.50) reflects a moderate change [31], which is consistent with previous digital mental health interventions in populations with psychological disorders [32]. This approach aligns with recommended practices in early-stage mHealth research, where the focus is on identifying potential signals of efficacy rather than definitive effect estimates [22]. Therefore, considering a 20% possible dropout [33], 50 women were estimated to need to be recruited to carry out the study. This approach is also coherent with previous studies adopting this type of methodology in the field of mHealth.

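### The sample-size paragraph calls 24 women sufficient, then reports a check that returns 41, and does not reconcile the two figures

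*Protocol article*

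**What the plan says.** Everything at issue is in one paragraph, under Sample Size in the protocol article.

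- It first gives a result from a nonparametric calculation that assumes non-normal data: "a sample of 24 women with BC diagnoses is sufficient when applying a Bonferroni-corrected significance level (α=.025"). Apart from α, nothing is stated for this calculation: no test, effect size or power.
- It then says that a calculation was run in two software packages to confirm the estimate, and reports: "The resulting sample size is 41 participants".
- For the second figure it lists five inputs. The change to be detected is "a mean difference between groups (eg, pre- and postintervention questionnaires) of 1.00". The SD is put at 2.00, which makes the standardised effect 0.50; α is .025 and power 0.80.
- The recruitment target follows: "considering a 20% possible dropout [33], 50 women were estimated to need to be recruited".

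The text does not remark on the gap between 24 and 41, and does not say that the first figure is withdrawn.

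**The concern.** A check that returns 41 does not confirm an estimate of 24. It is 17 women, or 71%, larger (41/24 = 1.71). As printed, the paragraph contains two incompatible statements of how many women are enough at the same α, and it presents the second as support for the first.

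The stake is how the results will be read. The Results section of the article names significant changes in psychological variables among the benchmarks for moving to a larger trial. If completion were poor, the sentence about 24 could be cited as showing that a small completer group was adequate, although the article's own listed inputs do not support that.

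A smaller matter is the step from 41 to 50, which does not quite return 41 women after the stated dropout.

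**Working it through.** **Inputs (all from Sample Size).** Mean difference 1.00; SD 2.00; so d = 1.00/2.00 = 0.50. α = .025; power = 0.80; dropout 20%; recruitment target 50. The design is a single group measured before and after. Sidedness is not stated.

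**Step 1: reproduce the 41.** For a paired t test with n pairs, the noncentrality parameter is d√n on n − 1 degrees of freedom. Two-sided power is the probability that a noncentral t variable falls beyond ± the critical value t(1 − α/2, n − 1).

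- n = 41: noncentrality 0.50 × √41 = 3.202; critical value 2.329; power 0.805.
- n = 40: noncentrality 0.50 × √40 = 3.162; critical value 2.331; power 0.793.

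The smallest n reaching 0.80 is therefore 41, as printed. A one-sided test at .025 would need 34, so the published figure is two-sided.

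**Step 2: put 24 through the same inputs.** This assumes that the inputs listed for 41 also apply to 24, because none are given for it.

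- n = 24: noncentrality 0.50 × √24 = 2.449; critical value 2.398; power 0.530.
- If α .025 is read as one-sided, power at 24 is 0.650.
- For 80% power at n = 24 with two-sided α .025, d would have to be about 0.67.

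**Step 3: does non-normality rescue 24?** The article says that the 24 assumed non-normal data, so Wilcoxon signed-rank power was simulated at n = 24, d = 0.50, two-sided α .025 (20,000 replicates per distribution):

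| Distribution of differences | Wilcoxon power, n = 24 |
|---|---|
| Normal | 50% |
| Logistic | 55% |
| Laplace | 64% |
| t with 3 df | 77% |
| Uniform | 44% |

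A separate, smaller simulation put the t with 3 df case at 78%. The sign test gave 20% to 72% across the same five distributions. None reaches 80%.

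**Step 4: dropout.** To keep n evaluable after a dropout proportion p, start with n/(1 − p).

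- 41/(1 − 0.20) = 51.25, so 52.
- 50 × (1 − 0.20) = 40, with power 0.793 from Step 1.
- The printed 50 agrees with 41 × 1.2 = 49.2 rounded up, or with 40/0.80 = 50.

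The shortfall is one evaluable woman, or about 0.7 percentage points below 80%.

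**The case against.** **Nothing rests on 24.** The target of 50 comes from the larger figure, and the paragraph frames the aim as looking for signals of efficacy. This stands. It limits the consequence but does not make the sentence correct.

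**The 53% borrows inputs.** This also stands. The article gives only α for the 24, so 53% is conditional. A larger assumed effect could give 24, but the reader is not told of one.

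**Nonparametric tests can be more efficient.** A reader might infer that a rank test must need more women than the t test, so that 24 is impossible on principle. That is not so: with heavy-tailed differences Wilcoxon can outperform the t test. What can be said is narrower: none of the distributions tried brings 24 to 80%.

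**The analysis threshold is .05.** Quantitative Analysis declares significance at P ≤ .05. At two-sided .05, 40 completers give 86.9% by paired t test. The shortfall at 40 therefore exists only at the α used for sizing. At n = 24 the .05 threshold gives 65.0%, so it does not rescue that figure.

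**Screen failures.** A reader might infer that the 50 are counted at consent, since "Participants will be required to sign an informed consent form during recruitment (phase 0") and psychological screening comes afterwards, so that far fewer than 40 would complete. The article does not establish this. Its use of recruited is ambiguous, its retention text concerns the 6-week programme, and no screening pass rate is given from which to calculate a loss.

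**Primary outcomes.** The calculation concerns pre-post change, which is secondary. A condensed article may leave precision for the usability outcomes to the full protocol, so its absence is not counted here.

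**Conclusion.** The point holds as an error of statement. The article says that 24 is sufficient and contradicts it with its own check. The 41 is right for a two-sided paired t test at α .025 with d = 0.50. Under the same inputs 24 gives about 53% power by paired t test, and about 50% to 78% by Wilcoxon for the normal and heavy-tailed distributions tried. These figures rest on carrying the inputs for 41 over to 24, the only option the text leaves.

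The dropout step is a minor slip: 40 evaluable rather than 41, and 79.3% rather than 80% at α .025.

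The documents do not support the stronger conclusion that the study as planned is seriously underpowered. The enrolment target follows from 41, not 24, and 40 completers come within a percentage point of the stated power.

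**What to change.** 1. Delete the sentence that 24 women are sufficient. Alternatively, give the test, effect size, power and sidedness behind it, and explain why it differs from 41.
2. State that 41 evaluable women give 80% power by two-sided paired t test at α .025 for d = 0.50.
3. State that 50 women starting the programme, with 20% dropout, give 40 evaluable and about 79% power on the same basis. This wording also settles the point at which the 50 are counted.

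The cost is a few reworded sentences. The enrolment target, design and procedures do not change. The stated power becomes very slightly less favourable, about 79% in place of 80%.

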### Study Outcomes

#### Primary Outcomes

The primary outcomes are UX and usability. They will be assessed using 4 questionnaires, namely, the User Engagement Scale-Short Form (UES-SF) [34], the System Usability Scale (SUS) [35], the Italian Chatbot Usability Scale, version B (ITA BUS B) [36], and the User Mobile Application Rating Scale (uMARS) [37]. They will be administered at different time slots throughout the study, in particular, at the end of week 3 (UES-SF, SUS, and ITA BUS B) and at the end of the study (week 6: UES-SF, SUS,; ITA BUS B, and uMARS; Textbox 2).

Summary of the questionnaires administered and their timing.
**Screening**
Kessler Psychological Distress Scale (K10)General Health Questionnaire (GHQ)Short Form Health Survey 36 (SF-36)
**At the beginning of the study (week 0)**
Perceived Stress Scale (PSS)Multidimensional Psychological Flexibility Inventory (MPFI)General Self-Efficacy Scale (GSE)Emotion Regulation Questionnaire (ERQ)Coping Orientation to Problems Experienced‐New Italian Version 25 (COPE-NVI-25)
**At the end of week 3**
User Engagement Scale-Short Form (UES-SF)System Usability Scale (SUS)Italian Chatbot Usability Scale, version B (ITA BUS B)
**At the end of the study (week 6)**
GHQPSSMPFIGSEERQCOPE-NVI-25UES-SF (this will be administered the following day so as not to burden the participant during completion)SUS (this will be administered the following day so as not to burden the participant during completion)ITA BUS B (this will be administered the following day so as not to burden the participant during completion)User Mobile Application Rating Scale (uMARS; this will be administered the following day so as not to burden the participant during completion)
**Follow-up (4 months after the conclusion)**
PSSQualitative interview

The end points to be measured include the scores of individual questionnaire items, the average scores of the questionnaires, and the differences between average scores of the questionnaires at various survey times. In addition, the participants’ experiences with the app and interactions with ALBA, as well as their use of the intervention, will be evaluated through semistructured interviews conducted 4 months after the study concludes. These interviews will collect qualitative data to supplement the primary outcome information.

#### Secondary Outcomes

The variables expressing the psychological well-being outcomes will be assessed by administering self-report questionnaires at the beginning (screening and week 0) and at the end (week 6) of the intervention (Textbox 2 provides a detailed overview of the questionnaire adopted). The end points to be measured include the scores of individual questionnaire items, the average scores of the questionnaires, and the differences between the average scores of the questionnaires at 2 survey times. In addition, the Perceived Stress Scale (PSS) [38] will be administered during a follow-up conducted 4 months after the study’s conclusion.

Both the clinical and usability tests will yield within-subject and between-subject comparison results.

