#### Secondary Objective

The secondary goal is to assess the efficacy of the intervention on women’s psychological well-being through the administration of self-report pretest-posttest and follow-up questionnaires.

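### The GHQ score that admits women to the study is also their only pre-intervention GHQ value, so in this single-arm design regression to the mean may pass for improvement; the size depends on GHQ scoring that the protocol leaves open.

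*Protocol article*

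**What the plan says.** The Inclusion criteria (Textbox 1) require women to "Have a general well-being score of ≥3 on the General Health Questionnaire". The screening set in Textbox 2 is "Kessler Psychological Distress Scale (K10)General Health Questionnaire (GHQ)Short Form Health Survey 36 (SF-36"). The week-0 set is "Perceived Stress Scale (PSS)Multidimensional Psychological Flexibility Inventory (MPFI)General Self-Efficacy Scale (GSE)Emotion Regulation Questionnaire (ERQ)Coping Orientation to Problems Experienced" (the 25-item Italian version); the GHQ is not in it. Phase 2 under Design and Study Plan also counts five questionnaires at week 0, which matches this list. The GHQ heads the week-6 list.

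Secondary Outcomes takes the well-being measures from "self-report questionnaires at the beginning (screening and week 0) and at the end (week 6) of the intervention" and makes the difference between two survey times an endpoint. Quantitative Analysis tests beginning against end within the one sample, at P≤.05. The Secondary Objective reads: "The secondary goal is to assess the efficacy of the intervention". The Results section counts significant psychological change among the benchmarks for moving to a larger trial.

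Two further passages bear on size. Psychological Assessment describes the GHQ-12 on a 4-point response scale with a maximum of 36. Entry also requires distress "defined by a score between 15.9 and 29.9 on the Kessler Psychological Distress Scale" and, on SF-36 Mental Health, to "Obtain a score between 30 and 80".

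**The concern.** A score that must exceed a cut on one occasion will on average be closer to the population mean on the next, even if nothing has changed. A fresh baseline taken after selection absorbs much of this fall. The other five psychological scales have such a baseline at week 0; the GHQ does not. Because there is no control arm, the fall cannot be estimated and subtracted afterwards, and no later analysis plan can recover a week-0 GHQ that was never collected.

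At stake is the GHQ pre-post result. It could reach significance in the direction of benefit with no effect of the app, be reported under an objective worded as efficacy, and contribute to a decision to proceed.

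**Working it through.** **1. The plan's own figure.** Sample Size gives a mean difference of 1.00, an SD of 2.00, α = .025 and power 0.80. A paired t test with d = 1.00/2.00 = 0.50 and two-sided α = .025 has power 0.805 at n = 41, so the stated 41 reproduces. The planned 0.50 is therefore in SDs of the difference. With 50 recruited and 20% dropout, 50 × 0.80 = 40 women complete.

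**2. Inputs.** From the protocol: GHQ cut of 3 or more, 40 completers, P≤.05. Assumed, because the protocol gives neither: the correlation r between screening and week 6 (.5 to .7) and the share of women passing the cut. Scores are treated as normal, with no true change.

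**3. Formulas**, for a cut k SD from the population mean:

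- λ = φ(k) / (1 − Φ(k))
- spurious shift = (1 − r)·λ, in population SDs
- variance of the selected screening scores: V = 1 + kλ − λ²
- SD of the difference = √[(1 − r)²·V + 1 − r²]
- shift in SDs of the difference: d = shift / SD of the difference
- chance of P≤.05: noncentral t, 39 df, noncentrality d·√40, two-sided .05

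**4. Worked case, half pass (k = 0).** λ = 0.798, V = 0.363. For r = .5, shift = 0.5 × 0.798 = 0.399; SD = √(0.25 × 0.363 + 0.75) = 0.917; d = 0.435; chance 77%. For r = .7, shift = 0.3 × 0.798 = 0.239; SD = √(0.09 × 0.363 + 0.51) = 0.737; d = 0.325; chance 52%.

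**5. Range over the share passing (GHQ cut only).**

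| Share passing | r | Shift (population SD) | d (SD of difference) | Chance of P≤.05 |
|---|---|---|---|---|
| 97% | .5 | 0.035 | 0.036 | 6% |
| 97% | .7 | 0.021 | 0.027 | 5% |
| 69% (k = −0.5) | .5 | 0.255 | 0.273 | 39% |
| 69% (k = −0.5) | .7 | 0.153 | 0.205 | 24% |
| 50% (k = 0) | .5 | 0.399 | 0.435 | 77% |
| 50% (k = 0) | .7 | 0.239 | 0.325 | 52% |

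**6. Which row applies.** On the 0–36 score, with an assumed mean of 13 and SD of 5.5, a whole-number score of 3 or more means exceeding 2.5: (13 − 2.5)/5.5 = 1.91, so about 97% pass. On a 0–12 score (an assumption; the protocol does not mention one) the same cut can exclude about half.

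**7. All entry limits together.** A zero-effect simulation applied the GHQ cut and the K-10 and SF-36 windows, with assumed means, SDs and correlations (r .5 to .8, 40 completers). On a 0–12 score, P≤.05 occurred in 25% to 82% where 43% to 57% passed the GHQ cut, and in 7% to 25% where 69% to 80% passed. On a 0–36 score it occurred in 5% to 16%. The extra limits reduced the fall in every 0–12 setting. On 0–36 they reduced it in some settings and increased it in others. Every setting moved towards apparent improvement.

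**The case against.** The strongest objection is that the protocol's own description of the GHQ makes the bias negligible: on a 0–36 score a cut of 3 excludes almost nobody. This stands as a limit on size. It does not settle the matter, because the criterion does not say which scoring it uses. Phase 1 under Data Collection presents a score below 3 as a mark of clearly good well-being, so the cut is meant to exclude someone.

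Second, the upper K-10 limit and the lower SF-36 limit remove the worst scorers and work against a one-sided fall. This also stands in part, as step 7 shows.

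Third, the GHQ is one of six psychological scales at week 6, under a secondary objective, and psychological change is one benchmark among several. The missing control group is admitted under Strengths, Limitations, and Future Directions. Elsewhere the text speaks of initial efficacy and of signals rather than definitive estimates. All of this is true and lowers the weight of the point. But no passage mentions regression to the mean, and admitting that there is no control group does not cover an avoidable choice of baseline.

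Fourth, one sentence under Phases 2 and 3 could mean that the screening scales are repeated at week 0. Textbox 2 and the count of five say otherwise, so the sentence needs reconciling.

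A reader might go further and infer that GHQ improvement is bound to appear at about the planned effect, or that K-10 and SF-36 would behave the same way. The documents support neither. The first needs a cut that excludes a large share of women. For the second, both windows are two-sided, so size and even direction depend on where they sit in the population.

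**Conclusion.** The point holds as a flaw in the measurement schedule: the truncated selecting score is the only pre-intervention GHQ value, and nothing in the design separates its expected fall from an effect of the app. The direction is towards apparent benefit. The amount runs from negligible (about 97% passing) to 0.24 to 0.40 population SD (half passing). In the unit of the planned 0.50, the latter is 0.32 to 0.44, or 65% to 87% of it. These figures rest on normal scores, r of .5 to .7, 40 completers and the GHQ cut alone.

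The change is worth making because it is cheap and cannot be made after data collection, but the point is moderate. It concerns one secondary scale. The five scales first given at week 0 are not selection variables and are touched only through their correlation with the screening scores, so it would be wrong to call the whole secondary objective biased to this degree.

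**What to change.** - Add the GHQ-12 to the week-0 set in Textbox 2 and change the count of five in Phase 2.
- Define GHQ change as week 6 minus week 0, and use the screening GHQ for eligibility only.
- State which GHQ scoring the cut of 3 refers to, and whether the outcome uses the same scoring.
- Reconcile the sentence under Phases 2 and 3 with Textbox 2. If K-10 or SF-36 is repeated as an outcome, give it a week-0 baseline under the same rule.
- In the Secondary Objective, describe the result as within-person change rather than efficacy. This is secondary to the new baseline but still needed: if scores fluctuate slowly, some regression will remain between week 0 and week 6.

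The cost is twelve extra items, once, in an app that already delivers five questionnaires at that visit, plus the edits to the text.
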